### Statistical analysis

2.11

Patient characteristics at baseline will be reported with descriptive statistics as means and standard deviation (SD), median and interquartile range (IQR), or numbers and percentages as appropriate. Normality will be visually assessed using histograms and the Shapiro–Wilk test.

Using intention‐to‐treat analysis, treatment effects, differences between groups and confidence intervals (95%) will be calculated through repeated‐measures ANOVA, examining the interaction between treatment groups (SE and NSE) over time (baseline, post‐intervention, and 6‐month follow‐up). If the ANOVA results are statistically significant, univariate analysis will be conducted using the Tukey *post hoc* test, with Bonferroni adjustment for multiple comparisons. Effect size will be calculated using Cohen's *d*, categorized as small (0.02), medium (0.05), and large (0.08) (Cohen, 1988). IBM SPSS Statistics (Version 21.0; IBM Corp., Armonk, NY, USA) will be used for all analyses.

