## Abstract

Exercise therapy is the most common approach for people with chronic neck pain (CNP). Although well‐established, it remains unknown which type of exercise is the best for treating this condition. Moreover, pain processing can play a role in the persistence of pain and in the response to interventions. Thus, the aim of this randomized controlled trial is to compare the acute and long‐term effects of two exercise protocols (specific and non‐specific) on pain and pain processing in individuals with CNP. One hundred and ten participants aged between 18 and 65 years who have had non‐specific neck pain for more than 3 months will be recruited. They will be randomized and allocated into two groups (specific exercises and non‐specific exercises) and both groups will perform an exercise programme twice a week for 8 weeks. Both programmes are divided into two progressive and individualized phases. The primary outcomes are change in pain intensity after 8 weeks of exercise and exercise‐induced hypoalgesia, and secondary outcomes are pressure pain threshold, temporal summation of pain, conditioned pain modulation, the Neck Disability Index, the Baecke Physical Activity Questionnaire, and the Global Perception of Change Scale. Outcomes will be assessed at baseline, after 8 weeks of intervention, and at 6‐month follow‐up.

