### Sample size

2.10

The sample size was calculated using G*Power 3.1.9.7 based on analysis of variance (ANOVA) repeated‐measures, within–between interactions (two groups and three measurements). Thus, this study is designed to detect a small effect size (eta square of 0.02; Daher et al., 2020) in pain intensity. To detect this difference, 41 participants in each group are needed (assuming a power of 0.80, α level of 0.05 and critical *F* = 3.052). Considering a 15% dropout, the study will include 94 participants, with 47 in each group.

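### The analysis is labelled intention-to-treat, but the three-visit repeated-measures ANOVA it names keeps only participants with all three visits unless missing values are imputed, and no imputation is stated

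*Protocol article*

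**What the plan says.** The Statistical analysis section fixes the population and the model in one sentence: "Using intention‐to‐treat analysis, treatment effects, differences between groups and confidence intervals (95%) will be calculated through repeated‐measures ANOVA". The model examines the group-by-time interaction "over time (baseline, post‐intervention, and 6‐month follow‐up"), and "IBM SPSS Statistics (Version 21.0; IBM Corp., Armonk, NY, USA) will be used for all analyses". The SPSS procedure is not named.

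The Sample size section uses the same structure, "within–between interactions (two groups and three measurements"), finds 41 per group, and then allows for loss: "Considering a 15% dropout, the study will include 94 participants, with 47 in each group".

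The Abstract places the primary pain outcome at 8 weeks: "The primary outcomes are change in pain intensity after 8 weeks of exercise and exercise‐induced hypoalgesia".

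The article does not mention imputation, a mixed model, or a rule for a participant who misses a visit.

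**The concern.** The label and the method do not fit together as written. Intention-to-treat is normally taken to mean that everyone randomised is analysed in the group to which they were allocated. A classical repeated-measures ANOVA (in SPSS, GLM Repeated Measures) deletes any participant who lacks one of the three values.

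The consequence falls on the primary pain outcome. Someone who gives a valid pain score at 8 weeks but misses the 6-month visit is also removed from the 8-week comparison. An observed primary endpoint is discarded because of a later, post-randomisation event. If that event is related to pain, and differently so in the two arms, the 8-week contrast is biased. The trial would then report as intention-to-treat an estimate that comes from completers.

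Arm-dependent loss is plausible but not established. The programmes are done at home, participants are not blinded, and the Introduction describes increased pain after specific exercise as a possible barrier to adherence. That remark concerns adherence to treatment, not attendance at visits.

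**Working it through.** **1. The plan's own sample size.** Inputs from the Sample size section: "this study is designed to detect a small effect size (eta square of 0.02"), "assuming a power of 0.80, α level of 0.05 and critical" *F* = 3.052, 2 groups, 3 measurements. The correlation between visits is not given; 0.5 is assumed.

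- f² = 0.02 / 0.98 = 0.0204, so f = 0.143.
- λ = f² × N × m / (1 − ρ) = 0.0204 × 82 × 3 / 0.5 = 10.04.
- df1 = (2 − 1)(3 − 1) = 2; df2 = (82 − 2)(3 − 1) = 160.
- Critical F = 3.0525; power = 0.809. N = 82 is the smallest even N that reaches 0.80.

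The stated 41 per group and the critical F both reproduce. Other correlations would require N = 112 (0.3), 66 (0.6) or 50 (0.7), so 0.5 is the value consistent with the stated figures.

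**2. How many are lost.** 94 × 0.15 = 14.1 participants, leaving 94 × 0.85 = 79.9, about 80.

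**3. Power (same formula, ρ = 0.5).**

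| Analysed | Power |
|---|---|
| 80 (completers) | 0.799 |
| 94 (all, no information lost) | 0.863 |

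The second row is an upper bound, because a mixed model cannot recover visits that never took place.

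**4. Precision at 8 weeks.** If 5% to 10% are already lost by week 8, about 89 to 85 of the 94 have a week-8 value. Restricting to 80 completers inflates the standard error by √(89/80) − 1 = 5.5% or √(85/80) − 1 = 3.1%.

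**5. Bias, by arithmetic.** In an arm that loses 15%, the full mean is 0.85 × completers + 0.15 × dropouts. The completer mean therefore differs from the full mean by 0.15 × d, where d is the difference between completers and dropouts. With random loss in the other arm, the group difference shifts by 0.15 × 0.5 = 0.08 points up to 0.15 × 2.5 = 0.38 points for d between 0.5 and 2.5 (assumed).

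**6. Bias, by simulation.** Assumptions: no true effect, NPRS SD 2, correlation 0.5 between baseline and week 8, all loss after week 8, log-odds of loss changing by 1 per SD of week-8 pain. The result is the between-group difference in change to week 8 among completers.

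| Dropout pattern | Spurious difference (points) |
|---|---|
| 15% per arm, informative in one arm only | about 0.13 |
| 15% per arm, opposite directions | about 0.27 |
| 10% against 20%, same dependence on pain | about 0.08 |
| 15% per arm, same dependence on pain | about 0 |
| One arm only, log-odds 0.5 per SD | about 0.07 |

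Against the 2.5-point MCID in the pain outcome section, 0.13 / 2.5 = 5% and 0.27 / 2.5 = 11%.

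Steps 4 and 6 are separate scenarios: step 4 has some loss before week 8, step 6 has none. All steps use 94 participants. The Abstract gives 110, which is a separate inconsistency; with 110, power would be 0.859 with about 93 completers against at most 0.914.

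**The case against.** The strongest objection is that a journal article commonly leaves missing-data handling to the full protocol or the SAP. An ANOVA on imputed data can carry the intention-to-treat label, and the label can also be read narrowly as analysis by allocated group. The dropout allowance does not settle the matter, since such inflation is routine whatever the missing-data method. This stands to the extent that a reader might infer that the planned analysis cannot be intention-to-treat; the document supports that only if nothing is imputed. What remains is not a missing section. The stated label and the stated model do not agree as written, and the narrow reading still leaves out randomised participants.

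A reader might also infer that dropouts disappear from every analysis. They do not. Baseline descriptives, adherence and adverse events do not need three visits, and the Global Rating of Change has no baseline value.

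Third, the bias may be negligible. Both arms follow home programmes of the same frequency, length and two-phase structure, and loss that acts alike in both arms gives a bias of about zero. The non-zero figures rest on assumed patterns and are small against the MCID. This stands, and it limits the severity.

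**Conclusion.** The point holds, conditional on no imputation. Followed as written, the repeated-measures analyses are complete-case analyses that would set aside about 14 of 94 participants at the planned dropout, including some with an observed 8-week pain score. The power cost is small (0.80 against at most 0.86, correlation 0.5 assumed). The possible bias at 8 weeks is about 0.13 to 0.27 NPRS points under the assumed informative, arm-dependent loss after week 8, and about zero under symmetric loss. The documents do not support saying that the primary result will be biased, only that the method leaves it open to avoidable selection under the wrong label. Severity: should be fixed.

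**What to change.** Replace the repeated-measures ANOVA with a likelihood-based linear mixed model (SPSS MIXED) that uses all observed visits of all randomised participants, grouped as randomised.

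- Enter baseline as one of the three repeated outcomes, with a common baseline mean across arms and an unstructured covariance. This keeps participants who have only a baseline value; a model with baseline as a covariate would drop them.
- Make the 8-week group contrast primary, and report the 6-month contrast as well.
- Add a sensitivity analysis for data not missing at random, for example one that shifts the values assumed for missing visits separately by arm.
- Keep the complete-case ANOVA only as a supportive analysis, labelled as such.

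Stating an imputation rule, or relabelling the population as complete cases, would also remove the contradiction. Relabelling would still discard observed 8-week scores.

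Cost: a change of analysis wording and slightly more analysis work, with the same software and data. The main model relies on data being missing at random, which is why the sensitivity analysis is needed. The change should be made before any unblinded analysis.

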On the other hand, non‐specific exercise (NSE), described as exercising the non‐painful area (Dueñas et al., 2021; Vaegter & Jones, 2020), seems to activate endogenous analgesic pathways (Naugle et al., 2012) and produce more EIH effects. It can be found in other chronic conditions such as knee osteoarthritis (Burrows et al., 2014) and shoulder myalgia (Lannersten & Kosek, 2010); however, in CNP, the EIH effect of NSE is not well established. In the last systematic review and meta‐analysis on this topic, Senarath et al. (2022) concluded that the evidence on EIH is conflicting and limited, caused by low methodological quality (Senarath et al., 2022; Vaegter & Jones, 2020). Besides this, SE cannot be considered superior to NSE in pain intensity and pain processing in CNP due to the small effect sizes and high risk of bias (Bontinck et al., 2024; Villanueva‐Ruiz et al., 2022), whether in acute or long‐term interventions (Hansen et al., 2022). It is also important to emphasize that the assessment of pain processing using QST, a method widely employed for this purpose (Xie et al., 2020), has not been well investigated in the area.

The primary aim of this randomized controlled trial (RCT) is to investigate if 8 weeks of NSE is superior in improving pain and EIH compared to SE in CNP. In addition, pain processing evaluated by QST will be compared between groups after the 8‐week intervention and at 6‐month follow‐up.

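### The primary pain outcome is change at 8 weeks, but the planned test is a three-visit interaction that gates the 8-week comparison, and the stated power belongs to the interaction

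*Protocol article*

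**What the plan says.** The abstract of the protocol article fixes the time point for pain: "The primary outcomes are change in pain intensity after 8 weeks of exercise". Exercise-induced hypoalgesia (EIH) is the other primary outcome. The Introduction gives the primary aim, which "is to investigate if 8 weeks of NSE is superior in improving pain and EIH compared to SE in CNP". Section 2.9.1, which defines the pain measure, names no time point.

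Section 2.11 analyses outcomes by repeated-measures ANOVA, "examining the interaction between treatment groups (SE and NSE) over time", with time meaning baseline, post-intervention and 6 months. It continues: "If the ANOVA results are statistically significant, univariate analysis will be conducted using the Tukey" post hoc "test, with Bonferroni adjustment for multiple comparisons". It does not say which ANOVA term has to be significant, how many comparisons the Bonferroni step covers, or whether the comparisons use raw visit scores or changes from baseline. It does say that between-group differences and 95% confidence intervals will be calculated, but ties them to no visit.

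Section 2.10 sizes the trial for the same interaction ("two groups and three measurements") at an "eta square of 0.02", power 0.80 and alpha 0.05. This gives 41 per group.

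**The concern.** For pain, the stated outcome is a single comparison: NSE against SE, change from baseline to 8 weeks. The planned test asks whether the groups differ in their course over any of three visits. That creates three problems.

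- The interaction can be significant because of a 6-month difference alone.
- A real 8-week difference must first pass the interaction test and then a corrected follow-up test, so the chance of declaring it is below the power quoted for the interaction.
- If no contrast is named as decisive, the interaction, the 8-week result and the 6-month result can each later be presented as the primary finding.

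The follow-up step is also confused. With two groups there is one between-group comparison per visit, so Tukey's method adds nothing there. In its standard form it is not suited to comparing correlated visits within a person. Bonferroni is an alternative to it, not a companion.

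**Working it through.** **Inputs.** From section 2.10: two groups, three measurements, eta squared 0.02, alpha 0.05, power 0.80, 41 per group, critical F 3.052. The documents give no SD, no correlation between visits and no effect pattern. I assume unit SD, equal correlation rho between visits (0.5, with 0.3 and 0.7 as the range), and that the interaction term opens the gate.

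**Step 1: the plan's own figure.** f² = 0.02/0.98 = 0.0204, so f = 0.143. For the within–between interaction, λ = f² × N × 3/(1 − rho), with 2 and 2(N − 2) degrees of freedom. At N = 82 and rho = 0.5, λ = 0.0204 × 82 × 3/0.5 = 10.04, critical F(2, 160) = 3.0525 and power is 0.809. The stated size reproduces. At rho 0.3 the same power needs N = 112, and at rho 0.7 it needs N = 50.

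**Step 2: the group difference this implies.** Let the between-group differences at the three visits, centred on their mean, be D. The interaction variance over the six cells is ΣD²/12. A difference d at one follow-up only, or equal at both, gives ΣD² = (2/3)d², so f² = d²/18 and d = √(18 × 0.0204) = 0.606 SD. If half remains at 6 months, ΣD² = d²/2, so λ falls to 0.75 × 10.04 = 7.53 and interaction power to about 0.68.

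**Step 3: no 8-week effect, 0.606 SD at 6 months only.** By simulation (40,000 trials, 41 per arm), the interaction is significant in 81% of trials at rho 0.5, 66% at rho 0.3 and 96% at rho 0.7. Gate plus 8-week comparison is then positive in about 1–5%, depending on the Bonferroni factor and form of comparison.

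**Step 4: a true 0.606 SD effect at 8 weeks, rho 0.5.** Closed forms for the direct tests with 41 per arm:
- Change score: noncentrality 0.606/√(2 × (1 − 0.5) × 2/41) = 2.74, power 0.77.
- Baseline-adjusted: noncentrality 0.606/√((1 − 0.5²) × 2/41) = 3.17, power about 0.87–0.88.

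Simulated power:

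| Procedure | 8 weeks only | Sustained | Half left at 6 months |
|---|---|---|---|
| Interaction F alone | 0.81 | 0.81 | 0.68 |
| Gate, raw 8-week score, Bonferroni 3 | 0.56 | 0.53 | 0.49 |
| Gate, raw 8-week score, Bonferroni 2 | 0.61 | 0.58 | 0.52 |
| Gate, raw 8-week score, no division | 0.68 | 0.65 | 0.58 |
| Gate, change score, Bonferroni 3 | 0.61 | 0.61 | 0.60 |
| Gate, change score, no division | 0.73 | 0.73 | 0.66 |
| Direct change-score test | 0.77 | 0.77 | 0.77 |
| Direct baseline-adjusted contrast | 0.88 | 0.87 | 0.87 |

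**Step 5: sensitivity to rho.** At 0.3 and 0.7 the gated route is also below both direct tests in every pattern. The baseline-adjusted contrast has about 0.81 at rho 0.3 and 0.96–0.97 at rho 0.7. The change-score test has 0.63 and 0.94.

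**The case against.** The protocol also aims at long-term effects and assesses three visits, section 2.9.1 fixes no time for pain, and the sample size and analysis agree with each other. All of this is true, and the sample-size calculation is not in error for the test it describes. But the only place that dates the primary pain outcome says 8 weeks, and no text makes the three-visit pattern the primary outcome. The unconditional promise of between-group differences with confidence intervals helps, but it does not say which one decides the trial.

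Four stronger readings are tempting and are not supported:

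- A reader might infer that a late-only effect would lead to a false 8-week claim. It rarely would. The significant interaction is then a true one, and the follow-up step yields an 8-week claim in only about 1–5% of trials.
- A reader might infer that Tukey plus Bonferroni corrects twice. For two groups at one visit Tukey applies no correction, so a double penalty is not demonstrated. The wording is confused and the number of comparisons is open.
- A reader might credit the whole rise to 0.87 to targeting 8 weeks. Part of it is baseline adjustment: the direct unadjusted change-score test has about 0.77.
- A reader might infer that the interaction F is always the weaker test. At 0.81 it exceeds the change-score test in two of the three patterns, and at 0.68 it falls below it only when the effect fades.

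**Conclusion.** The mismatch stands. The test named for pain does not answer the 8-week question, and the 0.80 power in section 2.10 does not apply to an 8-week claim. Under the planned route that claim has power of about 0.49–0.73 for the effect the sample size implies, against about 0.77 for a direct change-score test and 0.87 for a baseline-adjusted contrast.

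These figures rest on 41 analysed per arm, rho 0.5, equal correlations, a gate on the interaction and a Bonferroni factor of 1 to 3. The levels move with rho, but the ordering of the gated and direct 8-week tests does not. If another ANOVA term, such as the main effect of time, were allowed to open the gate, the gate could cost less; the text does not settle this. The point concerns pain only, not EIH.

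**What to change.** In section 2.11, name the primary pain test: the between-group difference in NPRS at 8 weeks, adjusted for baseline NPRS (ANCOVA, or the 8-week contrast of a mixed model). It should be two-sided with a 95% confidence interval and not conditional on the interaction. Make the 6-month contrast secondary. Replace the Tukey-and-Bonferroni sentence with one stated correction for secondary comparisons, giving the number of comparisons it covers. Set the alpha for the pain test consistently with EIH as second primary outcome. The 0.87 above is at two-sided 0.05, and a smaller share would lower it.

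In section 2.10, restate the power for the 8-week contrast at the same sample size, with the assumed SD and baseline correlation written out.

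The cost is more than a change of analysis wording, because the sample-size text must be rewritten and the 6-month pain result no longer contributes to the primary test. No additional data or participants are needed.

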##### Pain intensity at rest and on movement

Pain intensity will be evaluated through the numerical pain rating scale (NPRS) (Ferreira‐Valente et al., 2011). This scale ranges from 0 (no pain) to 10 (worst possible pain) and will be questioned at rest (Celenay et al., 2016) and different active cervical movements (flexion, extension, inclinations and rotations) (Rampazo et al., 2020). The highest value will be used for analysis. The minimal clinically important difference (MCID) is 2.5 points on a scale of 0–10 (Pool et al., 2007).

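### The cut-offs for Cohen's d are one tenth of the usual values and contradict the protocol's own use of small in the sample size section

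*Protocol article*

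**What the plan says.** Section 2.11 (Statistical analysis) of the protocol article names Cohen's d as the effect size measure and fixes its labels: "categorized as small (0.02), medium (0.05), and large (0.08"). It does not say whether d compares the two groups or measures change within a group, and it does not restrict d to one outcome. No other section gives different cut-offs.

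Section 2.10 (Sample size) uses the word small on another scale. The trial is designed to detect a "small effect size (eta square of 0.02") in pain intensity, in a repeated-measures ANOVA with "two groups and three measurements". It concludes that "41 participants in each group are needed", "assuming a power of 0.80, α level of 0.05 and critical" F of 3.052.

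For pain intensity, the primary outcomes section states a minimal clinically important difference (MCID) that "is 2.5 points on a scale of 0–10".

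**The concern.** All three cut-offs are lower than the standard scale for d by the same factor of ten, which looks like a slipped decimal. The error also shows without reference to any outside convention, because the effect that the trial calls small when it is planned would be called large when it is reported.

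What is at stake is the wording of the results. The trial compares two active exercise programmes and expects a small difference between them. If the labels are applied as written, sampling error alone will usually be enough to reach the top category, and the three categories cannot separate small from large effects.

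**Working it through.** **Inputs from the protocol article**
- Cut-offs for d: 0.02, 0.05, 0.08 (Statistical analysis).
- Design effect: eta squared 0.02, called small; power 0.80; alpha 0.05; two groups, three measurements; 41 evaluable per group (Sample size).
- Enrolment: "Considering a 15% dropout, the study will include 94 participants, with 47 in each group" (Sample size). The Abstract instead has "One hundred and ten participants aged between 18 and 65 years", or 55 per group. That figure is used here only to test sensitivity.
- Pain MCID: 2.5 points on a 0–10 scale.

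**Assumptions, not in the article**
- d is a between-group standardised difference.
- Pain SD of 1.5 to 2.5 points.
- For the reproduction in step 1 only: correlation of 0.5 between repeated measures and no sphericity correction.

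**Step 1. Reproduce the stated sample size.**
- f² = 0.02 / (1 − 0.02) = 0.0204, so f = 0.143.
- Noncentrality = f² × N × 3 / (1 − 0.5). At N = 82 this is 0.0204 × 82 × 3 / 0.5 ≈ 10.0.
- With 2 and 2 × (82 − 2) = 160 degrees of freedom, the critical F is 3.0525 and power is 0.809. N = 80 gives 0.799.
- So 41 per group and the critical F of 3.052 both reproduce. The eta squared of 0.02 was therefore really used as the design effect.

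**Step 2. Put the design effect on the d scale.**
- For two groups, d = 2f = 2 × 0.143 = 0.286.
- 0.286 / 0.08 = 3.6. The planned small effect is 3.6 times the threshold for *large*.
- With cut-offs of 0.2, 0.5 and 0.8, d = 0.286 is small and the two sections agree.

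**Step 3. How often would noise be labelled *large*?** With no true difference and n per group, d × √(n/2) follows a t distribution with 2n − 2 degrees of freedom. At n = 41 the standard error of d is √(2/41) = 0.22.

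| n per group | 0.08 × √(n/2) | P(abs(d) ≥ 0.08) | P(abs(d) ≥ 0.02) |
|---|---|---|---|
| 41 | 0.362 | 0.718 | 0.928 |
| 47 | 0.388 | 0.699 | 0.923 |
| 55 | 0.420 | 0.676 | 0.917 |

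The median |d| from noise alone is 0.15 at 41 per group and 0.14 at 47, already above the *large* cut-off.

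**Step 4. True effects and significant results.**
- With a true d of 0.2, about 81% of results would be labelled *large*; with 0.286, 87–89%; with 0.5, 98–99%.
- The smallest |d| that is significant at two-sided 0.05 is the critical t divided by √(n/2), which is 0.44 at 41 per group and 0.41 at 47. Both are more than five times 0.08, so every significant group difference would be labelled *large*.

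**Step 5. In pain points.** 0.08 × 1.5 = 0.12 and 0.08 × 2.5 = 0.20 points. Against the MCID of 2.5 points that is 4.8% to 8%.

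**Step 6. After correction.** With cut-offs of 0.2, 0.5 and 0.8 and no true difference, P(|d| ≥ 0.8) is 0.0005, 0.0002 and 0.0001 at 41, 47 and 55 per group. P(|d| ≥ 0.2) is still 0.37, 0.33 and 0.30, so even correct labels need the confidence interval beside them.

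**The case against.** The strongest reply is that the labels are only descriptive. They do not enter the sample size, the ANOVA, the error rate, the estimate or its interval. A uniform factor of ten looks like a typing slip, and a reader who is given d as a number can apply the right scale. All of this stands, and it limits the point to interpretation and reporting. It does not make the sentence right, because the article fixes these labels and nowhere corrects them.

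It might also be said that 0.02 belongs to the eta squared scale, where the Sample size section does call it small. But the analysis sentence attaches the three values to Cohen's d.

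Three stronger readings are tempting, and the article supports none of them:
- *Almost any result, including pure noise, would be called large.* Too strong for noise: about 28% of null results at 41 per group and 30% at 47 would fall below 0.08.
- *These labels are the only yardstick for the size of an effect.* The article gives an MCID for pain, a minimum detectable change for pressure pain threshold (155.73 kPa), an MCID of 7 and a minimum detectable change of 10.5 for the Neck Disability Index, and thresholds for the Global Rating of Change. The analysis section also promises group differences with 95% intervals.
- *The planned d is certainly between groups.* The text does not say. The percentages in steps 3 and 4 hold only on that reading; the contradiction between the two sections uses the two-group conversion but none of those probabilities.

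**Conclusion.** The cut-offs are wrong as written, and they conflict with the Sample size section, where an effect equivalent to d of about 0.29 is called small. If d is between groups, 68–72% of null comparisons and all significant ones would carry the label *large*. The result hardly depends on which of the two stated enrolment figures is right. The figure of 0.12–0.20 pain points rests on an assumed SD and serves only to show the scale.

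This is a reporting error that should be fixed. It gives no ground for doubting the sample size, the test or the estimates.

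**What to change.** In Statistical analysis, replace the three cut-offs with 0.2, 0.5 and 0.8. This changes one sentence and needs no new data, recalculation or change of analysis.

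Two additions would help but are not needed to correct the error: state whether d is between or within groups, and say that the pain difference and its 95% interval will be read against the 2.5-point MCID already given.
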